#### **6.5.1. Patients who withdraw consent**

Unless the participant specifically withdraws consent for their data and samples to be stored, all data and samples that have already been collected from them will continue to be stored as per the original participant consent. This will also apply to participants who are unable to confirm enduring consent due to loss of capacity.

#### **6.5.2. Managing/replacing patients who withdraw early**

Participants who decide to withdraw will be invited to complete a withdrawal form which will be stored in the TMF (although refusal to do so will be respected). Participants who are withdrawn by the CI will be recorded in a Withdrawal Log that documents the enrolment number, participant initials, reason(s) for withdrawal and treatment offered (if applicable). A copy of the log will be retained in the CRF which will also directly capture information on withdrawal outcome (Discontinuation due to Adverse Event or Elective Withdrawal). Withdrawal Log originals will be stored in the TMF. Participants who withdraw or are withdrawn pre-randomization will be classified as screening failures (see section 6.3.4). Participants who withdraw or are withdrawn post-randomization (see section 6.5) will be classified as withdrawals and will not be replaced.

## **7. STUDY BLINDING**

### **7.1. Type of blinding**

Treatment groups will be allocated in a double-blind manner. Participants will be blinded to the treatment they receive (placebo or IMP) throughout all stages of the study. Investigators will also be blinded to the treatment until all samples have been collected and processed. Blinding will be generated by the dedicated trials pharmacy representative who has signed/dated the staff delegation log and is not otherwise associated with this study.

### **7.2. Procedure for production and maintenance of blind**

Blind production and maintenance will be according to dedicated trials pharmacy guidelines.

### **7.3. Breaking the blind in an emergency**

In an emergency (e.g. participant AE) the blind may be broken to determine whether this may be treatment-related. Blinding for previously collected or future treatments will not be compromised.

## 8. STUDY TREATMENTS

### 8.1. General information on the products (trial drugs) to be used

| IMP                      | Dosage form and strength | Manufacturer |
|--------------------------|--------------------------|--------------|
| AZD4017                  | Tablets 200 mg           | AstraZeneca  |
| Placebo to match AZD4017 | Tablets                  | AstraZeneca  |

Please refer to the IB for more information.

### 8.2. Frequency and duration of the trial drugs

Participants will be randomised to receive either AZD4017 400mg twice daily (as close to 12 hours apart as possible) or placebo. AZD4017 or placebo will be dosed as 2 tablets orally twice daily for 35 days starting at the baseline visit (Visit 1).

### 8.3. Administration/handling of the trial drugs

The AZD4017 tablets and matching placebo will be supplied to the dedicated trial pharmacy by Almac in bottles of 32, 200mg tablets with a unique kit number (sufficient for 8 days per bottle); 4 bottles will be dispensed at Visit 1 and 1 bottle will be dispensed at Visit 4 (sufficient for 5 days overage per participant). Almac will provide the pharmacy with a kit list to refer to when dispensing for each patient and a set of code breaks for emergency unblinding.

Participants will be instructed to take the AZD4017 or placebo tablets 30min before or at least 2 hours after a meal. In the case of vomiting or diarrhoea after taking the tablets, participants will be instructed not to repeat the dose but to wait for their next scheduled dose.

#### 8.3.1. Handling, storage and supply

Labels will be prepared in accordance with Good Manufacturing Practice (GMP) and local regulatory guidelines. The labels will fulfil GMP Annex 13 requirements for labelling. Label text will be in English. The labels will have a peel-off portion, which will be inserted into the participant's source data verification document at dispensing.

All study medications will be kept in a secure place under appropriate storage conditions. The IMP label on the pack specifies the appropriate storage.

#### 8.3.2. Drug accountability

The IMP provided for this study will be used only as directed in the study protocol. The study personnel will account for all IMP dispensed to and returned from the participants.

AstraZeneca personnel or its representative CTRU will ensure accountability logs are maintained for all study drugs received at the site, unused study drugs and for appropriate destruction. If possible, the study drug will be destroyed locally by the site pharmacy. Certificates of delivery and destruction will be signed and stored in the pharmacy site file.

#### **8.4. Prior and concomitant illnesses**

Participants and their GP will be requested to report any prior or concomitant illness and these will be assessed on an individual basis as to the most appropriate subsequent actions to be taken (if any) based on the exclusion and withdrawal criteria described above.

We do not anticipate that ADZ4017 will adversely affect any prior or concomitant illness.

#### **8.5. Prior and concomitant medications**

We do not anticipate that AZD4017 will adversely affect any prior or concomitant medications; however, certain medications are prohibited as they may interfere with study outcome measures.

##### **8.5.1. Permitted prior medications**

Participants will be allowed to receive any treatment that is judged to be in their best medical interests. Participants and their GP will be requested to report any new treatment and participants may be withdrawn according to exclusion and withdrawal criteria.

##### **8.5.2. Prohibited prior medications**

No specific drug interactions have been reported for AZD4017. However, the following medications are listed in the exclusion criteria as they may interfere with data integrity:

- Any topical, systemic (including vaginal/rectal) or inhaled GC treatment at the time of or within 3 months prior to the screening visit as this may affect 11 $\beta$ -HSD1 activity and secondary outcome measures
- Any anticoagulant medication (blood thinning e.g. warfarin) as this may reduce blood clotting and delay WH
- Probenicid or similar (for gout) as this may increase AZD4017 excretion

##### **8.5.3. Permitted concomitant medications**

Participants will be allowed to receive any treatment that is judged to be in their best medical interests.

##### **8.5.4. Prohibited concomitant medications**

Please refer to exclusion criteria.

### 8.5.5. Surgical procedures

We do not anticipate that AZD4017 will adversely affect any prior or concomitant surgical procedures but as a precaution patients will be ineligible to participate in the event of any medical/surgical procedure (excluding skin biopsy) or trauma during IMP administration or within one week following the last administration of the IMP as judged by the CI.

### 8.6. Special warnings and precaution for use

AZD4017 has been studied in healthy human volunteers some patient groups and is generally well tolerated.

The most commonly reported AE amongst healthy volunteers were gastrointestinal disorders and headache and were of mild to moderate intensity. Please refer to IB for more information.

In a multiple ascending dose study (see IB for details) 30 healthy male subjects received single doses of AZD4017 followed by repeated doses of 75 mg once daily up to 900 mg twice daily for 9 days. The expected inhibition on 11 $\beta$ -HSD1 enzyme activity in liver measured by prednisolone generation in plasma after an oral prednisone challenge as well as on urinary GC metabolites was observed. An activation of the HPA axis was also indicated as an increase in both adrenocorticotrophic hormone (ACTH) and dehydroepiandrosterone sulphate levels while cortisol and testosterone levels were unchanged. A few subjects had transient increases in ALT and AST at 1-1.5xULN. One subject taking 1200mg once daily experienced an increase in ALT to 3x ULN. In all cases, liver transaminases returned to baseline on withdrawal of study drug. There is **no clear relationship with plasma exposure as the subjects with the highest ALT did not have the highest plasma area under the curve of either AZD4017** or the glucuronic acid metabolite.

In a Phase IIa trial of subjects with raised intraocular pressure, 7 subjects receiving 200mg AZD4017 once daily and 19 subjects receiving 400mg AZD4017 twice daily for up to 28 days, **no deaths or SAE were reported**; in the group receiving AZD4017 400 mg twice daily three subjects had ALT between 1 and 1.5x ULN, four subjects had AST between 1 and 1.5x ULN, two subjects had gamma-glutamyl transferase between 1 and 1.5x ULN and one subject had GGT between 1.5 and 2x ULN. An activation of the HPA-axis was demonstrated by an increase in ACTH and dehydroepiandrosterone sulfate levels. However, cortisol and testosterone levels were unaffected. No AEs associated with these findings were reported. In the clinical studies performed so far no obvious muscle effects have been seen.

Non-clinical data and observations in previous clinical studies with similar and even higher repeated doses of AZD4017 support dose administration according to the proposed clinical study protocol. Further information regarding non-clinical data and previous clinical studies can be found in the AZD4017 IB.

Blood samples will be taken at screening, baseline, days 7, 28, 35 and follow-up to monitor HbA1c, lipids, liver, kidney, thyroid and adrenal function.

## 8.7. Dose modifications

We do not anticipate any requirements for dose modifications.

## 8.8. Assessing subject compliance with study treatment(s)

Participants will be asked to complete a daily Diary Card indicating the time of treatment (at approximately 12h intervals).

The administration of all study medication will be recorded directly into the CRF as the expected number of tablets remaining, the actual number of tablets remaining, the overall percentage compliance  $((140 - (\text{actual number of doses remaining} - \text{expected number of tablets remaining})) / 140) * 100$  and the cumulative percentage compliance  $(1 - ((\text{actual number of tablets remaining} - \text{expected number of tablets remaining}) / (\text{visit day} \times 4))) * 100$  at Visits 2-6. Any missed tablets will be documented in the medical notes, along with reasons for the missed tablets.

Percentage Diary Card completion will also be recorded in the CRF (number of doses recorded divided by the total available number of doses and multiplied by 100) along with a copy of the Diary Card. Diary Card originals will be stored in the TMF.

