## **13.6. Definition of 'per protocol' set**

In addition to an intention-to-treat analysis including all patients, a supplemental 'per protocol' analysis (including only those who adhered to the treatment regimen of the programme they were allocated, did not violate the trial protocol in any substantial way, and have data available) will be performed. Prior to unblinding of the study, patients will be allocated to or excluded from the 'per protocol' set by a panel including the clinical project manager, trial statistician, and other appropriate clinical study team members.

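### The overall-compliance formula in sections 8.8 and 12.4.1 subtracts tablets from doses, and its fixed denominator of 140 is valid only at the end of treatment

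*Protocol*

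**What the plan says.** Section 8.2 sets the regimen: "AZD4017 or placebo will be dosed as 2 tablets orally twice daily for 35 days". Section 8.3 sets the supply, in "bottles of 32, 200mg tablets with a unique kit number": "4 bottles will be dispensed at Visit 1 and 1 bottle will be dispensed at Visit 4". It describes this as five days of overage.

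Section 8.8 has the CRF record expected and actual tablets remaining, and two percentages derived from them. The first is overall compliance, with a fixed denominator of 140. Its bracket takes the "actual number of doses remaining" and subtracts the "expected number of tablets remaining". The second is "the cumulative percentage compliance", which uses tablets in both terms and divides by visit day × 4. The sentence ends by naming Visits 2 to 6. Section 12.4.1 repeats both formulas.

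Section 4.2 lists percentage compliance over the treatment phase as a feasibility variable. Section 13.6 defines the per-protocol set as "including only those who adhered to the treatment regimen of the programme they were allocated", together with no substantial protocol violation and available data. It gives no percentage threshold and does not name a compliance formula.

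**The concern.** There are two separate defects.

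- **Units.** The bracket subtracts a tablet count from a dose count. The companion formula in the same sentence uses tablets in both terms, so the protocol is inconsistent with itself.
- **Denominator.** The 140 is the full-course total and does not change by visit. Before day 35, tablets that are not yet due are scored as if they had been taken.

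Both errors push the score upwards. What is at stake is the adherence figure that helps to judge whether a larger trial is feasible (section 13.4.4), and possibly the information put before the panel that allocates participants to the per-protocol set. Section 8.9.1 keeps non-compliant participants in the trial, so the compliance record matters for identifying them.

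**Working it through.** **Inputs.** Section 8.2: 2 tablets × 2 per day = 4 tablets per day for 35 days. Section 8.3: 4 × 32 = 128 tablets at Visit 1 and 32 at Visit 4. Visit days are 2, 7, 28, 30 and 35.

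**The plan's own figures.** 4 × 35 = 140 tablets, which is 70 doses, so 140 is a tablet count. Supply is 128 + 32 = 160 tablets, leaving 160 − 140 = 20, or 20/4 = 5 days. This agrees with section 8.3.

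**Formulas.** Let A be the actual and E the expected tablets remaining, and d the visit day.

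- Overall, literal (doses = A/2): (140 − (A/2 − E))/140
- Overall, tablets throughout: (140 − (A − E))/140
- Cumulative: 1 − (A − E)/(4d)

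**Literal reading at Visit 6 (E = 20).**

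- All 140 taken, A = 20: (140 − (10 − 20))/140 = 150/140 = 107.1%
- 120 taken (85.7%), A = 40: (140 − (20 − 20))/140 = 100.0%
- 70 taken, A = 90: (140 − (45 − 20))/140 = 115/140 = 82.1%
- None taken, A = 160: (140 − (80 − 20))/140 = 80/140 = 57.1%

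**Tablet reading, nothing taken.** A − E is then the number of tablets due so far, 4d.

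- Visit 2: (140 − 8)/140 = 94.3%
- Visit 3: (140 − 28)/140 = 80.0%
- Visit 4: (140 − 112)/140 = 20.0%
- Visit 5: (140 − 120)/140 = 14.3%
- Visit 6: (140 − 140)/140 = 0%

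**All visits.** Scores in %, for true intake of 100 / 50 / 0% of the tablets due. The Visit 4 count is assumed to come before the fifth bottle is dispensed; only the literal column depends on this.

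| Visit (day) | Dispensed | E | Overall, literal | Overall, tablets | Cumulative |
|---|---|---|---|---|---|
| 2 (2) | 128 | 120 | 142.9 / 141.4 / 140.0 | 100 / 97.1 / 94.3 | 100 / 50 / 0 |
| 3 (7) | 128 | 100 | 135.7 / 130.7 / 125.7 | 100 / 90.0 / 80.0 | 100 / 50 / 0 |
| 4 (28) | 128 | 16 | 105.7 / 85.7 / 65.7 | 100 / 60.0 / 20.0 | 100 / 50 / 0 |
| 5 (30) | 160 | 40 | 114.3 / 92.9 / 71.4 | 100 / 57.1 / 14.3 | 100 / 50 / 0 |
| 6 (35) | 160 | 20 | 107.1 / 82.1 / 57.1 | 100 / 50.0 / 0 | 100 / 50 / 0 |

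The literal and tablet columns are alternative readings of one formula, so their figures should not be combined. The literal reading is wrong at every visit, the tablet reading is right for every participant only at Visit 6, and the cumulative formula is right throughout.

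**The case against.** The strongest reply is that this is a one-word slip. The CRF items named in section 8.8 are tablets remaining, with no field for doses remaining; 140 is a tablet count; and the companion formula uses tablets. Staff would have to halve a recorded count to obtain the literal figures, and a score of 142.9% at Visit 2 would be noticed. Read in tablets, the Visit 6 formula is (140 − (A − 20))/140 = (160 − A)/140, which is already tablets dispensed less tablets returned, over 140. The 94.3% and 80.0% would also sit beside a recorded cumulative 0%. All of this stands, and it limits the harm. It does not make the printed formula right, and it leaves the fixed 140 at Visits 2 to 5. The visit range could be attached to the cumulative measure alone, but the plain reading covers both, and the unit error remains either way.

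A reader might infer that non-adherent participants will be classed as adherent and enter the per-protocol analysis. The protocol does not support that. Section 13.6 sets no cut-off and does not name this formula; a panel decides before unblinding, and it could also draw on tablet counts, the cumulative figure, diary cards and recorded reasons for missed tablets.

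Nor does a participant who takes every tablet to day 7, stops and is never counted again show a fault peculiar to this formula. The cumulative figure would also stay at 100%. Without a day-28 biopsy, that participant would fail the data-availability condition for a per-protocol analysis of the primary endpoint.

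It is also not established that the reported feasibility figure will be inflated, because section 4.2 does not say which percentage will be summarised.

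**Conclusion.** The formula is wrong as written in both sections. Taken literally, it overstates adherence at Visit 6 by 7.1 percentage points for a fully adherent participant (107.1 − 100), 32.1 for one who took half (82.1 − 50) and 57.1 for one who took none. Read in tablets, Visit 6 is correct and the error is confined to Visits 2 to 5. It is largest early on: 94.3% and 80.0% at Visits 2 and 3 for a participant who took nothing.

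These sizes rest on the stated dosing and supply, and on counts taken exactly on the scheduled days. The intention-to-treat primary analysis is untouched, and true adherence can be recovered from the recorded tablet counts. The exposure is to the adherence feasibility outcome and possibly to the per-protocol panel's judgement, because the protocol offers two percentages and does not say which is used. The correction should be made, but the point does not threaten the trial's main conclusion.

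**What to change.** In sections 8.8 and 12.4.1:

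- Change 'doses' to 'tablets' in the overall formula.
- Record the 140-denominator figure once, at the end of the planned 35 days, as (tablets dispensed − tablets returned)/140. Perfect adherence then gives (160 − 20)/140 = 100%.
- Count tablets not taken after early discontinuation as not taken. A participant who takes everything to day 7, stops and returns 100 of the 128 tablets scores (128 − 100)/140 = 20%.
- Use only the cumulative formula at Visits 2 to 5.
- State that these corrected figures feed the feasibility summary and the per-protocol review.

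The cost is two formula edits and a CRF or spreadsheet change, with no new data collection. Reported adherence may look less favourable.

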## 8.9. Withdrawal of treatment

### 8.9.1. Subject compliance

Participants will not be withdrawn on grounds of non-compliance in accordance with recent European Medicines Agency to avoid the presence of unobserved measurements as much as possible.

### 8.9.2. Lack of efficacy

Efficacy will be evaluated after termination of recruitment and a lack of efficacy will therefore not affect participant withdrawal.

## 9. METHODS OF ASSESSMENT

### 9.1. Assessment of primary variable (AZD4017 efficacy)

#### 11 $\beta$ -HSD1 activity in skin

To evaluate efficacy of oral AZD4017 on 24 hour 11 $\beta$ -HSD1 activity in skin, 3mm punch biopsies will be obtained at Visits 1 and 4 from lower outer forearm (midpoint between wrist and elbow) performed under local anaesthetic (e.g. lidocaine). This procedure will be conducted by authorised trial personnel according to the staff delegation log and does not require sutures. Administration of local anaesthetic may involve a momentary stinging sensation after which the procedure is pain-free. 11 $\beta$ -HSD1 activity assays will be conducted by the Scientific Lead within 8h as previously described [19]. To prevent accidental

unblinding, 11 $\beta$ -HSD1 activity samples will be stored frozen until the blind is broken at the end of the trial and will then be batch processed. Approximately 10% of the sample will be used for validation using a cortisol Enzyme Linked Immunosorbent Assay. Raw data (enrolment number, visit number and date) will be copied in its original form to secure server storage and recorded in the CRF as % conversion of cortisone to cortisol per hour.

## **9.2. Assessment of secondary variables**

### **9.2.1. Efficacy**

#### **9.2.1.1. Global 11 $\beta$ -HSD1 activity**

Systemic 11 $\beta$ -HSD1 activity will be inferred from urinary [THF+alloTHF]/THE ratios. These will be measured in 24 hour urine samples at Visits 1 and 6 by liquid chromatography–mass spectrometry. Samples will be taken using commercially available collection containers, frozen in aliquots and stored at -80°C in the WTBB designated storage area before batch shipping for analyses by the Institute of Metabolism and Systems Research (University of Birmingham) at the end of the trial. The original report generated for each sample will be stored in the TMF and recorded in the CRF at the end of the trial.

Measurements will be used to examine associations between participant systemic GC levels and outcome measures of skin function.

#### **9.2.1.2. AZD4017 in plasma and skin**

Skin samples will be collected at Visit 4 and blood plasma at visit 6 and stored at -80°C in the WTBB designated storage area before batch shipping for AZD4017 pharmacokinetic analysis by York Bioanalytical Solutions Ltd after the end of the trial. Blood samples will be collected by authorised research nurse support. Shipping contents, collection and delivery will be recorded and stored in the TMF. The original report generated for each sample will be stored in the TMF and recorded in the CRF.

### **9.2.2. Safety**

AE-related participant withdrawals (i.e. number of Discontinuations due to Adverse Events) e.g. exceeding hepatic/renal stopping criteria, myocardial infarction or stroke, inpatient hospitalization or any other AE deemed by the clinical care team to require trial withdrawal will be recorded as a Discontinuation due to Adverse Event under withdrawal outcome in the CRF. The following safety measures will also be used to assess AZD4017 safety:

#### **9.2.2.1. Clinical evaluation of biopsy site**

Following punch biopsies, participants will be requested to monitor the wound for any excessive adverse reaction (e.g. redness, rash, swelling or pain) and report any concerns to their GP. During Visits 2, 3, 4, 5 and 6, the application site will also be assessed by authorised trial personnel for signs of infection, detailed in the medical notes and recorded directly into the CRF as pass or fail.

#### 9.2.2.2. Body mass index

BMI is an attempt to quantify the amount of tissue mass (muscle, fat, and bone) in an individual, and then categorize that person as underweight, normal weight, overweight, or obese based on that value. BMI is defined as the body weight divided by the square of the body height, and is universally expressed in units of  $\text{kg/m}^2$ , resulting from mass in kilograms and height in metres. Height will be measured in metres to the nearest centimetre (e.g. 1.63m) and weight will be measured in kilograms to the nearest 100 grams (e.g. 60.2kg). Split values will be rounded up (e.g. 1.625m to 1.63m and 60.15kg to 60.2kg). BMI will be calculated using the formula:  $\text{BMI} = \text{weight (kg)} / \text{height (m)}^2$  and rounded up to two decimal place (e.g.  $\text{BMI} = 60.2 / 1.63^2 = 22.66$ ). Commonly accepted BMI ranges are underweight: under 18.5  $\text{kg/m}^2$ , normal weight: 18.5 to 25, overweight: 25 to 30, obese: over 30. Measurements will be conducted at Visits 1 and 6 by a qualified member of staff who has signed/dated the staff delegation log and weight, height and BMI will be recorded directly into the CRF.

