**10.8. Visit 6 (day 35) at CAH LMBRU**

We will monitor the biopsy site and participants will return 24 hour urine samples for storage until processing. Participants will be asked if anything has changed since the previous visit and if they have experiences any AE. Measures will be conducted as follows: 1) BMI, BP, waist-hip ratio 2) skin hydration 3) epidermal barrier function 4) 7 day barrier recovery time-point 5) sudomotor function 6) blood samples for HbA1c, lipids, FBC, LFT, U+E, thyroid and adrenal function, serum/plasma biobank storage and AZD4017 quantification 7) remaining tablets and diary cards will be returned to the pharmacy 8) wound imaging by OCT 9) skin thickness 10) payment

Blood tests results from all visits will be sent to the CI or authorised delegated personnel for immediate consultation, signature and dating. Signed and dated blood reports will be stored in the medical notes and recorded in the CRF as pass or fail.

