##### **13.4.2.2. Safety**

Safety analyses will be conducted in all patients who received any study treatment, according to treatment received. Continuous safety variables (BMI, waist-hip ratio, BP, HbA1c levels, lipids, FBC, LFT, eGFR, U+E, adrenal and thyroid function test) will be summarized descriptively by patient group at each timepoint. Unadjusted and adjusted summaries (adjusted for gender, age and baseline HbA1c) for absolute values and changes from baseline will be presented; between-group differences in absolute values and changes from baseline will be presented together with 90% confidence intervals. Adjusted summaries will be obtained via a linear regression model which mirrors analysis of covariance. Where necessary, transformations to a normal distribution will be performed. Where applicable, numbers of patients in each group whose values exceeded ULN (or were below the lower limit of normal) during the trial will be presented, corrected for exposure by 100 patient years.

Line listings of all AEs will be provided in the end of trial report. The frequency of all AE during the study period will be presented for each treatment group separately within classes of AEs defined by CTCAE preferred term. The data will be displayed as number of subjects experiencing the AE, percentage of subjects, and number of AE. AE will also be summarized by severity and relation to IMP. For recurrent AEs, the most severe occurrence will be recorded per AE per patient. AE data will also be corrected for exposure by 100 patient-years. For expected AEs the recorded rates will be compared against the rates outlined in the IB.

In addition to the above, the proportions of patients who passed the overall assessment of blood safety will be summarised using absolute and relative frequencies at each visit, in all patients and by treatment group at days 0, 7, 28, 35 & 42.

No inferential testing will be conducted; safety will be assessed in terms of the clinical relevance of the AEs reported and of any observed differences between groups.

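### Change in BMI to day 35 includes avoidable height-reading error, because height is measured again at Visit 6 to the nearest centimetre

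*Protocol*

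**What the plan says.** Protocol section 9.2.2.2 sets the resolution of both measurements. For height: "Height will be measured in metres to the nearest centimetre (e.g. 1.63m". For weight: "weight will be measured in kilograms to the nearest 100 grams (e.g. 60.2kg". Ties go upwards: "Split values will be rounded up (e.g. 1.625m to 1.63m and 60.15kg to 60.2kg".

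The same section sets the timing, "Measurements will be conducted at Visits 1 and 6 by a qualified member of staff", and the record, "weight, height and BMI will be recorded directly into the CRF". Table 1 and section 10.8 repeat BMI at day 35; the Visit 6 list opens "1) BMI, BP, waist-hip ratio 2) skin hydration 3) epidermal barrier function 4) 7 day barrier recovery time-point". No sentence says that the Visit 1 height is reused at Visit 6, so the plain reading is that each BMI uses that visit's own height.

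Section 13.4.2.2 names BMI first among the analysed measures: "Continuous safety variables (BMI, waist-hip ratio, BP, HbA1c levels, lipids, FBC, LFT, eGFR, U+E, adrenal and thyroid function test". Body weight is not in that list. For these variables, "between-group differences in absolute values and changes from baseline will be presented together with 90% confidence intervals".

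**The concern.** Over 35 days an adult's height is constant for practical purposes. If the two recorded heights differ, the difference is reading error. Because BMI divides by height squared, the error passes into BMI at about twice its relative size. Height is also recorded coarsely compared with weight.

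The change in BMI therefore mixes true weight change with height error, and a patient whose weight is unchanged can show a BMI gain or loss. Since weight itself is not a listed analysis variable, change in BMI is the planned summary of change in body mass. What is at stake is the precision of one descriptive safety summary in a trial of 15 per arm.

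**Working it through.** **The plan's own figure.** BMI = weight / height². For the example in 9.2.2.2, 60.2 / 1.63² = 22.658, which rounds to the stated 22.66. The formula is applied correctly.

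**Effect of one 1 cm recording difference.** The change in BMI is w/(h − 0.01)² − w/h² when the second height is 1 cm lower, or w/h² − w/(h + 0.01)² when it is 1 cm higher. One kilogram moves BMI by 1/h². The ratio gives the equivalent weight. The first row is the protocol's example; the other body sizes are illustrative.

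| Weight, height | BMI shift for 1 cm (kg/m²) | BMI shift for 1 kg | Equivalent weight (kg) |
|---|---|---|---|
| 60.2 kg, 1.63 m | 0.275 to 0.281 | 0.376 | 0.73 to 0.75 |
| 80 kg, 1.70 m | 0.323 to 0.329 | 0.346 | 0.93 to 0.95 |
| 90 kg, 1.70 m | 0.363 to 0.370 | 0.346 | 1.05 to 1.07 |
| 110 kg, 1.70 m | 0.444 to 0.452 | 0.346 | 1.28 to 1.31 |

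A worked case: 92.5 kg at both visits, with 1.70 m then 1.69 m, gives 32.01 then 32.39. That is +0.38 kg/m², or 0.38 / 0.346 = 1.1 kg, with no weight change.

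**Typical error per patient.** This needs inputs that are not in the protocol. I assumed a reading-error SD (s) of 0.3, 0.5 or 0.7 cm at each visit, mean BMI 32, height with mean 170 cm and SD 9 cm, and a weight-change SD of 1 or 1.5 kg.

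In closed form, rounding to 1 cm adds variance of about 1/12 cm² per reading. The SD of the difference between two recorded heights is therefore √[2(s² + 1/12)], and the SD passed into BMI change is about (2 × 32 / 170) times that. For s = 0.5 cm: √[2(0.25 + 0.083)] = 0.82 cm, and 0.82 × 0.376 = 0.31 kg/m². A weight-change SD of 1 kg contributes about 0.346 kg/m². The total is √(0.346² + 0.31²) = 0.46, which is about a third larger.

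Simulation agrees. The recorded height differs between visits in 34%, 51% and 63% of patients for s = 0.3, 0.5 and 0.7 cm. The per-patient error SD is about 0.22, 0.31 and 0.40 kg/m², or about 0.6, 0.9 and 1.2 kg. At s = 0.2 cm it is about 0.5 kg.

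**Effect on the 90% interval.** The half-width is t × SD × √(2/15), with t = 1.701 on 28 df, that is 0.621 × SD.

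| Weight-change SD | s (cm) | SD of BMI change, one height → re-measured | Half-width | Increase | Wider by |
|---|---|---|---|---|---|
| 1 kg | 0.3 | 0.351 → 0.415 | 0.218 → 0.258 | 0.040 | 18% |
| 1 kg | 0.5 | 0.351 → 0.467 | 0.218 → 0.290 | 0.072 | 33% |
| 1 kg | 0.7 | 0.351 → 0.536 | 0.218 → 0.333 | 0.115 | 53% |
| 1.5 kg | 0.3 | 0.526 → 0.571 | 0.327 → 0.355 | 0.028 | 8% |
| 1.5 kg | 0.5 | 0.526 → 0.610 | 0.327 → 0.379 | 0.052 | 16% |
| 1.5 kg | 0.7 | 0.527 → 0.665 | 0.327 → 0.413 | 0.086 | 26% |

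**With one height at both visits** the height term disappears from the change. What recording precision leaves is weight rounding: at most 0.1 kg, or 0.1 / 1.70² = 0.035 kg/m².

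**The case against.** Several points count against giving this much weight, and most of them stand.

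- *Size.* A reader might infer that every patient's BMI change carries error worth about 1 kg. The documents do not support that. About 1 kg is the effect of one full 1 cm difference in a patient of 80 to 90 kg. At s = 0.3 cm, two thirds of patients show no height difference at all. Rounding alone adds nothing when both readings fall in the same centimetre.
- *Bias.* A reader might infer that the safety comparison is distorted. The error is random and should be alike in both arms of a double-blind trial, so it widens the interval without shifting the group difference. Visit 1 uses two locations and Visit 6 one, so a difference between stadiometers is conceivable. The protocol does not say where the baseline height is taken, and a constant offset would cancel between arms to a close approximation.
- *Consequence.* Section 13.4.2.2 plans no inferential testing of safety. No withdrawal criterion, proof-of-concept rule or future sample-size estimate uses BMI. Absolute BMI, the other half of the planned summary, is barely affected because differences between patients are far larger.
- *Recoverability.* Weight and height are both recorded, so weight change, or BMI on the Visit 1 height, can be derived afterwards.
- *Place.* The height used in a derived variable could be settled in the statistical analysis plan, which is not at hand.

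The last point stands only in part. The protocol itself fixes the repeat measurement, its resolution, the formula and the visits, and as written these put error into the analysed change.

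**Conclusion.** The point holds as a minor matter of precision. Followed as written, section 9.2.2.2 puts height-reading error into a change that section 13.4.2.2 analyses. The direction is certain, and the effect of a single centimetre is exact arithmetic.

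The overall widening is driven wholly by assumption: the range of 8% to 53% comes from the assumed reading-error and weight-change SDs, and a careful reading technique would put it lower. In absolute terms the loss is small, and nothing the trial decides depends on it. It is worth correcting only because the correction is free.

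**What to change.** In section 9.2.2.2, state that height is measured at Visit 1 only and that BMI at both visits is calculated from that height. Only weight is then needed at Visit 6. The Visit 6 height field in the CRF can be dropped.

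The cost is one sentence, with one measurement fewer per patient and no loss of information. If Visit 6 heights have already been collected, the same rule can be applied at analysis from the recorded weights and Visit 1 heights.
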